**Fig 3 pone.0302480.g003:**
[figure not shown]
Illustration of the experimental protocol timeline. BMI: body mass index; PACES: physical activity enjoyment scale; OGTT: oral glucose tolerance test; IS: insulin sensitivity.

Subjects’ participation will be discontinued in case of withdrawn consent, or in case the interval between sessions is higher than 28 days. We will report reasons for withdrawal and discuss the reasons qualitatively in the final manuscript. Adverse events related or nonrelated to the research protocol experienced by participants during study (e.g. skeletomuscular injury, having a cold, etc.) will be carefully recorded and reported in the final manuscript.

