### Statistics

#### Sample size

The sample size was calculated from the literature [10, 12, 16, 17, 19, 23, 26, 27, 77] using the G*Power program (Heinrich-Heine-Universität Düsseldorf, Germany, version 3.1.9.6), inserting the parameters for a one-way ANOVA, effect size of 0.6 probability of error type alpha of 0.05 and power (probability of error type 1 –beta) of 0.9. With these parameters, 14 individuals will be needed (actual power of 0.93). Due to the usual sample loss of 25–40%, we will initially recruit 20 participants. In order to promote participant retention, frequent text messages will be sent as reminders to follow the instructions, and to show up in the scheduled sessions. Also, in case the participant misses a session, all effort will be made to reschedule as long as it is within 28 days of the previous session. Dropout reason will be recorded and reported in the manuscript.

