#### Data analysis

To ensure confidentiality, all study-related information will be stored securely at the study site. All participant information will be stored in locked file cabinets in areas with access controlled by the principal investigator ([name]). All laboratory specimens, reports, data collection, process, and administrative forms will be identified by a coded ID number only to maintain participant confidentiality. All records that contain names or other personal identifiers, such as locator forms and informed consent forms, will be stored separately from study records identified by code number. No personal information from participants will be released outside the study. Full access to the complete dataset will be permitted only to [name] and to [name].

The statistical analysis will be conducted following the principles of intention-to-treat analysis [78]. Thus, data from subjects will be assessed as randomized, regardless of whether they received the randomized treatment, meaning that even if they fail to follow the physical activity and diet pre- and post-session instructions, or fail to complete the sessions as required (e.g. fail to achieve 9–10 in the OMNI scale), or fail to perform the OGTT at the schedule time, so-called non-adheres, their data will be included in the analyses. Furthermore, we will analyze the data “per protocol” [79], meaning that participants who deviate from instructions will be excluded from final analyses. Differences in results stemming from intention-to-treat and per protocol analyses will be discussed accordingly. The available variables will also be compared between participants who withdraw from the study and those who remain. Incomplete datasets (e.g., participant who complete 1 or 2 of the 3 sessions) will analyzed via sensitivity analysis of augmented data sets. Dropouts will be included in the analysis by modern imputation methods for missing data [80].

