Data will be expressed as the mean and standard deviation with a confidence interval of 95%. For the analysis of data normality, we will perform the Shapiro-Wilk test. For normally distributed data, analysis of variance will be used with one source of variation (experimental situation). If a significant main effect was observed, post hoc Tukey test was used. For non-parametric data, the Kruskal-Wallis test was used, or Friedman’s test, when necessary. Effect size was calculated and interpreted as follows: <0.2 = no effect, 0.2–0.49 = low effect, 0.5–0.79 = medium effect, and greater than 0.8 = large effect [81, 82]. The significance level will be 5%. The Prisma program (GraphPad Software, San Diego, CA-USA–version 8.4.0) will be used to analyze the results. The trial will be reported following the CONSORT guidelines [83, 84].

As stated above under **Blinding procedures**, the researcher responsible for data analysis (the statistician) will be blinded for group allocation. For that, a collaborator outside the research team will double enter data coded for allocation into a computer in separate spreadsheets so that the researcher responsible for data analysis can assess data without having access to information about the allocation. Allocation will only be revealed after statistics are run. In case there are doubts about data entry (missing values, or values outside the reference range), the researcher responsible for data analysis will contact the collaborator outside the research team responsible for double entry of the data to check accuracy. There will be no interim analysis.

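### Dropouts are to be imputed and partial completers kept for a sensitivity analysis, but the named tests, as stated, neither use partial sessions nor carry imputation uncertainty; a mixed model on observed sessions would avoid both problems

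*Protocol article*

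**What the plan says.** The Data analysis section of the protocol article commits to intention-to-treat, with a per-protocol analysis alongside. Two sentences deal with missing sessions. On partial completers: "Incomplete datasets (e.g., participant who complete 1 or 2 of the 3 sessions) will analyzed via sensitivity analysis of augmented data sets". On dropouts: "Dropouts will be included in the analysis by modern imputation methods for missing data [80]".

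The same section then fixes the tests. For normally distributed outcomes it is an analysis of variance with experimental condition as the only factor, followed by: "If a significant main effect was observed, post hoc Tukey test was used". Otherwise it is Kruskal-Wallis or, when needed, Friedman. No participant, period or sequence term is named, nor any model that accepts one or two sessions from a participant, nor any step for combining results over imputed datasets.

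The Sample size section expects substantial attrition: "Due to the usual sample loss of 25–40%, we will initially recruit 20 participants".

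**The concern.** This is a three-session crossover with about 20 participants, so each partial completer matters. Two features of the text do not fit together.

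- **Partial data.** Participants with one or two observed sessions hold real information on the condition effects. The named tests either need all three values (repeated-measures ANOVA, Friedman) or ignore the pairing within a participant (one-factor ANOVA, Kruskal-Wallis). The text gives partial completers a place only in a sensitivity analysis.
- **Imputed data.** When a completed dataset is passed to one of these tests, the filled-in values count as observed. Unless the analysis is repeated over several imputations and pooled, the error term is too small and its degrees of freedom are too many.

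The level or the power of the primary comparison is at stake, depending on which ANOVA is run. How many imputations to use is a detail that an analysis plan could settle. The point here is the pairing that the protocol itself states: imputation with tests that, as described, have no way to reflect it.

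**Working it through.** **1. The plan's own figure.** The Sample size section uses G*Power with a one-factor ANOVA and these inputs: "effect size of 0.6 probability of error type alpha of 0.05 and power (probability of error type 1 –beta) of 0.9". The result reported there is: "14 individuals will be needed (actual power of 0.93)". Take 0.6 as Cohen's f with three conditions.

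- Independent groups, 14 per group: λ = f² × N = 0.36 × 42 = 15.12, df 2 and 39, power 0.928. This reproduces 0.93.
- 14 in total over three independent groups: λ = 0.36 × 14 = 5.04, df 2 and 11, power 0.40.
- Repeated measures, 14 participants: λ = 0.36 × 14 × 3/(1 − ρ), df 2 and 26. Power is 0.917 at ρ = 0 and 0.998 at ρ = 0.5.

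The stated power matches an independent-groups ANOVA, so the literal one-factor reading of the analysis cannot be dismissed. The crossover design and the mention of Friedman point to repeated measures. Both readings are carried below.

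**2. How much would be missing.** Of 20 recruited:

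| Loss | Dropouts | Completers |
|---|---|---|
| 25% | 5 | 15 |
| 30% | 6 | 14 |
| 40% | 8 | 12 |

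At 40%, completers fall below the required 14. Assume that all loss follows randomisation and that dropouts complete one or two sessions with equal chance, so 1.5 are missing on average. The missing sessions are then 5 × 1.5 = 7.5 of 60 (12.5%), or 8 × 1.5 = 12 of 60 (20%).

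**3. Why one completed dataset misleads.** A repeated-measures ANOVA on 20 complete rows claims (20 − 1)(3 − 1) = 38 error degrees of freedom. The observed sessions support fewer. At 40% loss it is 48 − 20 − 2 = 26; at 25% loss it is about 52.5 − 20 − 2 = 30.5.

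**4. Simulation.** These assumptions are not in the documents: 20 randomised, SD 1, within-participant correlation 0.6, dropout unrelated to outcome, one or two sessions completed. The alternative has condition means 0, 0.35 and 0.70.

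| Analysis | Type I error, 25% / 40% loss | Power, 25% / 40% loss |
|---|---|---|
| Single imputation, no random draw, repeated-measures ANOVA | 0.127 / 0.202 | not comparable (level not held) |
| Single imputation with random draw, repeated-measures ANOVA | 0.112 / 0.155 | not comparable (level not held) |
| Single imputation with random draw, literal one-factor ANOVA | 0.008 / 0.013 | 0.42 / 0.45 |
| Complete cases, repeated-measures ANOVA | 0.047 / 0.050 | 0.73 / 0.61 |
| Multiple imputation (20 sets), pooled repeated-measures ANOVA | 0.044 / 0.033 | 0.78 / 0.71 |
| REML mixed model, observed sessions only | 0.047 / 0.038 | 0.79 / 0.75 |

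With no missing data, repeated-measures ANOVA has power of about 0.86. Over correlations of 0.5 to 0.7, single imputation with repeated-measures ANOVA gives about 9–14% at 25% loss and 15–21% at 40%. The literal one-factor ANOVA gives about 0.2–2%. Monte Carlo error is about 0.5 to 1.5 percentage points.

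The simulated mixed model had no period term. Adding one costs two more error degrees of freedom (26 − 2 = 24 at 40% loss).

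**The case against.** The strongest reply is that the protocol does not say single imputation. It cites a reference for up-to-date methods, and the number of imputations and the pooling rule commonly sit in an analysis plan that is not shown. With proper pooling, the repeated-measures ANOVA holds its level, and at 25% loss its power (0.78) is practically that of the mixed model (0.79). This stands. A reader might infer that the named tests cannot carry imputation uncertainty. That is too strong: ANOVA F tests and contrasts can be pooled, and only Tukey and rank tests lack an equally standard route.

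Other stronger inferences also fail.

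- **That up to 40% of participants would be imputed.** The 25–40% is planned loss from recruitment. Under Random allocation the sequence is revealed only after the strength tests, which follow five familiarization sessions, so some loss may precede randomisation. Imputing 40% of sessions (24 of 60) needs all eight dropouts to be randomised and complete none.
- **That the main result certainly rests on imputed values.** The text never labels a primary analysis. The sentence on dropouts suits the intention-to-treat commitment, but this remains a reading.
- **That false positives are certain.** Under the literal one-factor ANOVA the error goes the other way.
- **That the withdrawal rule contradicts intention-to-treat.** Study type and design ends participation "in case the interval between sessions is higher than 28 days". Data analysis governs data already collected. Ending participation does not discard earlier sessions, so the two are compatible.

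What remains is the stated pairing. No listed test uses a participant's one or two sessions as a paired contribution, and no pooling step accompanies the imputation.

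**Conclusion.** The concern holds in a conditional form. As written, the plan combines imputation of dropouts with complete-data tests and gives partial completers only a sensitivity role. The consequence depends on the reading:

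- one completed dataset with repeated-measures ANOVA: roughly two to four times the nominal 5%;
- one completed dataset with the literal one-factor ANOVA: a test near 1% whose power is about half that of repeated-measures ANOVA on full data;
- multiple imputation properly pooled: the level is held.

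The documents do not settle which applies, so none of these figures is a prediction for this trial. The sizes rest on an assumed correlation of 0.5–0.7, on all 20 being randomised, on dropouts completing one or two sessions, and on dropout unrelated to outcome. The case for changing the plan does not need the worst figure. The mixed model held its level in both settings and matched or slightly exceeded pooled imputation in power. It gained 6 points over complete cases at 25% loss (0.79 against 0.73) and 14 at 40% (0.75 against 0.61). This should be changed before analysis.

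**What to change.** Make the primary intention-to-treat analysis a REML linear mixed model on every observed session, whether a participant has one, two or three. Use condition and period as fixed effects and participant as a random effect, without imputation. Take the pairwise condition comparisons from that model. Report participants who have no OGTT, with reasons, but do not impute them. Keep multiple imputation as a sensitivity analysis only, applied to the same model's contrasts and pooled by Rubin's rules. Reword the two missing-data sentences so that the primary and sensitivity roles are explicit.

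The cost is revised analysis wording and possibly different software; conduct, visits and sample size are unaffected. The mixed model relies on sessions being missing at random, which these data cannot verify. The planned comparison of participants who withdraw with those who remain should therefore stay.

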### Primary blood outcomes–OGTT-derived indexes

After ~9–10 hours of overnight fasting and ~10–11 hours after each experimental session, participants will report to a local clinical laboratory, and a blood sample will be collected (minute 0). Then, they will ingest 75 grams of glucose in 300 ml of water, and blood samples will be collected every 30 minutes until 120 minutes after glucose ingestion, totaling 5 withdrawals (minute 0, minute 30, minute 60, minute 90, and minute 120). Plasma concentrations of glucose, insulin, and C-peptide (a marker of insulin production) will be analyzed in each sample. With the insulin and glucose results at minute 0 (fasting values), insulin resistance will be calculated using HOMA-IR with the formula glucose (mmol) x insulin (μU/ mL) ÷ 22.5 [63], and insulin sensitivity using the quantitative insulin sensitivity check index [64]. Several insulin sensitivity indexes will be derived from the OGTT data [28], such as the oral glucose insulin sensitivity index [65], the Matsuda insulin sensitivity index [66] and Cederholm’s index [67], muscle insulin sensitivity index [68, 69], glucose-stimulated insulin sensitivity index [21], Gutt index [70], Avignon et al. index [71], Belfiore et al. index [72], Stumvoll et al. index [73], and McAuley et al. index [74], the simple index of insulin sensitivity [75], and as an index of hepatic insulin resistance, the hepatic insulin resistance index [68]. In addition, the glucose, insulin, and C-peptide AUC will be calculated using the trapezoidal method [76].

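### A Shapiro-Wilk test on about 14 participants decides between ANOVA and rank tests for 17 related primary outcomes, so methods may differ between them and the rank branch gives no effect estimate with CI

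*Protocol article*

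**What the plan says.** The Data analysis section sets the rule: "For the analysis of data normality, we will perform the Shapiro-Wilk test. For normally distributed data, analysis of variance will be used", with experimental condition as the only source of variation. For the rest: "For non-parametric data, the Kruskal-Wallis test was used", with Friedman's test as an alternative whose use is not defined. No transformation is named for any outcome. On presentation, the section says: "Data will be expressed as the mean and standard deviation with a confidence interval of 95" per cent. An effect size is planned separately.

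The section on primary blood outcomes lists 14 sensitivity or resistance indexes and 3 areas under the curve (glucose, insulin, C-peptide), all from one five-sample glucose tolerance test per session. One index formula is printed: "insulin resistance will be calculated using HOMA-IR with the formula glucose (mmol) x insulin", divided by 22.5. The Study type and design section describes a three-condition crossover. The Sample size section plans for 14 participants, recruits 20 and expects a loss of 25 to 40%.

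**The concern.** This rule is written into the plan and applies to the primary outcomes. It is not a detail left for later.

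A significance test on so few participants separates normal from moderately skewed data poorly, so chance largely settles the branch. Seventeen outcomes built from the same measurements could then be split between mean-based and rank-based analyses. A reader could not tell whether two indexes disagree because of biology or because of the method.

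The two rank tests named give a p-value but no treatment effect with an interval, so results in that branch cannot be set beside the others on a common scale. At least one index is a product of glucose and insulin, so a multiplicative scale is plausible, and the plan offers no log-scale analysis. If that scale is the right one, some power is given up.

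**Working it through.** **Inputs from the protocol article.** N = 14; three paired conditions; 5% level; 14 + 3 = 17 outcomes under the primary heading. Completers expected from 20 recruited: 20 × 0.75 = 15 down to 20 × 0.60 = 12.

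**Assumptions (not in the document).** A log-normal index; total log-SD 0.4 to 0.6, with 0.25 as a low-spread case; within-person correlation 0.7; a 35% difference between the extreme conditions, with the third halfway. The gate is taken to fire if any of the three conditions has Shapiro-Wilk p < 0.05.

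**1. The plan's own figure.** Reading the effect size as Cohen's f = 0.6, with three groups of 14, the noncentrality is 0.6² × 42 = 15.12 on 2 and 39 degrees of freedom. Power is 0.928, which matches the stated 0.93. That calculation presumes the ANOVA branch and allows nothing for a rank test.

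**2. How the gate behaves.** At n = 14, a single Shapiro-Wilk test rejects normality for a truly log-normal variable with probability 0.24, 0.36 and 0.46 at log-SD 0.4, 0.5 and 0.6. With three conditions checked, the rank branch is taken in 0.53, 0.66 and 0.78 of trials. If residuals are tested instead, the gate fires in only 15 to 36% of trials. The article does not say which is meant.

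**3. Power at log-SD 0.5.**
- Log-scale repeated-measures ANOVA: 0.69
- Raw-scale repeated-measures ANOVA, no gate: 0.61
- Gate with Friedman as the fallback: 0.59

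The total gap is 0.69 − 0.59 = 0.10. Of this, 0.69 − 0.61 = 0.08 comes from the scale and 0.61 − 0.59 = 0.02 from the gate. Over log-SD 0.4 to 0.6 the total gap is about 8 to 11 points.

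**4. Other variance splits.** Log effects 0 / 0.12 / 0.25, 3,000 simulated trials per row:

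| Between / within log-SD | Log-scale | Raw, no gate | Gate + Friedman | Log minus gated | Raw minus gated |
|---|---|---|---|---|---|
| 0.4 / 0.2 | 0.801 | 0.743 | 0.718 | 0.083 | 0.025 |
| 0.5 / 0.2 | 0.814 | 0.699 | 0.690 | 0.124 | 0.009 |
| 0.6 / 0.25 | 0.606 | 0.459 | 0.479 | 0.127 | −0.020 |
| 0.5 / 0.3 | 0.462 | 0.356 | 0.368 | 0.094 | −0.012 |

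The gap to the log-scale analysis is 8 to 13 points here. Against raw-scale ANOVA the gated rule ranges from 2.5 points worse to 2 points better. In these four settings raw-scale ANOVA and Friedman disagree on significance in 19 to 24% of trials, so the branch taken can change the conclusion.

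**5. Type I error.** With no effect, the gated rule with Friedman rejects in 0.046 to 0.051 of trials.

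**6. Low spread.** At log-SD 0.25 the log-scale advantage almost vanishes. Part of the reason is that either analysis then detects a 35% difference nearly every time, so this case says little about smaller effects.

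**The case against.** The strongest reply is that the power figures do not indict the gate. They come from data simulated as exactly log-normal, which favours a log analysis by construction, and the document gives no distribution, SD or within-person correlation for any index. The only printed formula is a product; the others are not shown, so skewness across the whole list cannot be checked. This stands. The power loss is conditional, and it is attributed mainly to the scale.

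Several stronger readings are tempting, and the document does not support them:
- **Raw values are tested.** The text speaks only of data normality. It does not exclude residuals, so the 53 to 78% gate rates describe one reading of the plan.
- **The Kruskal-Wallis loss belongs here.** With that fallback, power in the four settings of the table falls to between 0.12 and 0.37. That comes from ignoring the crossover pairing, a separate defect, and Friedman is also listed.
- **A promised interval is not delivered.** The 95% interval in the plan belongs to a descriptive summary, available whichever test is used. The narrower point remains: the rank tests named give no interval for the treatment effect.
- **Incomplete participants are lost.** The same section plans imputation for dropouts and a sensitivity analysis for incomplete data sets, so rank tests could be run on completed data.

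None of these replies removes the inconsistency of method across related primary outcomes.

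**Conclusion.** The point holds in a limited form. The plan fixes a data-driven choice of test, based on about 14 participants, for 17 related primary outcomes. Methods may therefore differ between near-duplicate measures, and the rank branch supplies no treatment effect with CI. This part needs no assumption about skewness. How often methods would be mixed cannot be computed from the document, because the outcomes are correlated and the object of the normality test is not stated.

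The power cost is conditional on log-normality: about 8 to 11 points for the gated rule with Friedman against a log-scale within-participant analysis at log-SD 0.4 to 0.6, and almost none at 0.25 for the effect studied. A reader might infer that the gate causes this loss or produces false positives. The simulations support neither: the gate accounts for roughly 2 points either way, and Type I error stays near 5%. The plan is weakened but not invalidated.

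**What to change.** Remove the Shapiro-Wilk gate and pre-specify one within-participant model for all blood outcomes: repeated-measures ANOVA, or a linear mixed model with a participant effect.

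List in advance which outcomes are log-transformed: those that are products or ratios involving insulin, and the insulin and C-peptide areas under the curve, provided that values are positive and not already on a log scale. Report these as ratios of geometric means with 95% CI, and the remaining outcomes as mean differences with 95% CI from the same model. Judge the fit from residual plots. Keep Friedman, not Kruskal-Wallis, as a sensitivity analysis.

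The cost is wording only, with no extra participants or measurements. The downside is that log-scale effects are read as percentage rather than absolute differences, which makes direct comparison with published absolute changes harder.

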## Objective

### Primary objective

The primary objective will be to investigate the acute effects of high- and low-volume strength exercise sessions on insulin sensitivity indexes in obese adults.

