### Study type and design

This study will be a randomized controlled, crossover, 3-arm, clinical trial. The protocol description followed the SPIRIT [40] and the TIDieR [41] guidelines (Fig 1 and S1–S3 Tables). Participants will undergo a health history questionnaire, anthropometric measures which include height, body mass, waist circumference and body composition, a period of familiarization and strength assessment. At least 4 days after the strength tests, they will carry out 3 randomized experimental sessions, separated by at least 4 (but no more than 28) washout days, as it has been shown that the acute effect of exercise on improved insulin action lasts up to 2 days [42]. In case the sessions are scheduled 21 to 28 days apart, participants will be required to perform a familiarization session 2 weeks after the preceding (and 1 to 2 weeks before the following) experimental session to avoid defamiliarization. The interval between experimental sessions will be recorded and reported in the final manuscript, and discussed accordingly. To avoid the variation in insulin sensitivity across the menstrual cycle [43–49], in case premenopausal women are included in the sample, they will be assessed in the follicular phase (days 1–14) [9, 26, 50–52] of their menstrual cycle. Two of the experimental sessions will be performed with strength exercises: a high-volume session [3 sets per exercise–high volume]; a low-volume session [1 set per exercise–low volume]; and a control session: no exercise. In the exercise sessions, 7 exercises will be performed for the major muscle groups (1 –hex bar squat; 2 –bench press; 3 –leg press; 4 –lat pulldown; 5 –leg extension; 6 –shoulder press; 7 –leg curl; Fig 2), totaling 21 sets in the high-volume session and 7 sets in the low volume session [24]. The sessions will be held at night, between 8:00 pm and 9:00 pm. This time schedule for the sessions is ecologically valid, as exercise in the evening is commonly observed in fitness centers due to time constraints for exercising earlier during the day [13, 53], and it has been shown that night-time exercise does not affect sleep duration or quality [53]. The next morning between 7:00 am and 8:00 am (between 10 and 11 hours after the session), an OGTT will be performed in a local clinical laboratory. Participants will respond to scales of feeling, enjoyment, and self-efficacy after the exercise sessions. All sessions will be supervised by a certified fitness professional. The experimental design is illustrated in Fig 3.

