## Discussion

### Potential impact and significance of the study

An acute bout of strength exercise has been shown to improve insulin action and glucose metabolism [23]. However, current guidelines for the prescription of strength exercise suggest that 8 to 30 sets could be performed [25], which means a ~4-fold difference in exercise volume and thus time commitment. Furthermore, high-volume strength exercise might discourage individuals with low self-efficacy, which might diminish long-term adherence to a training program. Therefore, assessing the effects of low- vs high-volume strength exercise on insulin action and glucose metabolism bears clinical relevance because if low-volume strength exercise elicits improvement in these parameters, individuals might be more motivated and feel more confident in performing low-volume strength exercise.

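### Cheap improvement: with exactly three conditions, Tukey after a significant omnibus test is valid but needlessly conservative; closed testing would recover power at the same 5% family-wise error

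*Protocol article*

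**What the plan says.** The Study type and design section states: "This study will be a randomized controlled, crossover, 3-arm, clinical trial". Every participant does a high-volume, a low-volume and a control session, so each index has three pairwise contrasts: high versus control, low versus control, and high versus low.

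For normally distributed data, the Data analysis section uses ANOVA with the experimental condition as the single factor, and then: "If a significant main effect was observed, post hoc Tukey test was used". The significance level is 5%. The non-normal branch (Kruskal-Wallis or Friedman) names no pairwise procedure and is not part of this point.

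The Sample size section derives 14 participants by "inserting the parameters for a one-way ANOVA, effect size of 0.6 probability of error type alpha of 0.05 and power" of 0.9, with an actual power of 0.93. It gives no power for any single contrast.

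The Primary objective is to "investigate the acute effects of high- and low-volume strength exercise sessions on insulin sensitivity indexes in obese adults", which treats the two volumes alike.

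**The concern.** The pairwise rule is written into the article, so it can be judged as it stands and is not a gap left to an unseen analysis plan. Tukey's critical value protects all three comparisons at once without needing any prior test. Here it is applied only after an omnibus test that, with three conditions, already supplies the protection needed for unadjusted pairwise tests. The trial therefore pays for protection it could have had at a lower price.

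The stake is power for the individual contrasts in a small crossover. One result becomes more likely than it need be: high versus control significant and the other two contrasts not. That pattern is hard to interpret. It could be taken to mean that low volume does not work, or that low volume does not differ from high, and it supports neither.

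**Working it through.** **1. The plan's own figure.** Effect size 0.6 is read as Cohen's f (the metric is not named), with three conditions and 14 observations in each. Noncentrality = f² × total observations = 0.36 × 42 = 15.12. On 2 and 39 df at 5% the power is 0.928, which matches the stated 0.93. As a repeated-measures test with zero within-person correlation (2 and 26 df) it is 0.917. Both are powers of the omnibus test.

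**2. Why unadjusted pairs are enough after the gate.** If any two of the three pairwise nulls are true, all three means are equal, so the third is true as well. Only three cases can arise:

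- All three means equal: an error needs the omnibus test to reject, probability at most 5%.
- Exactly one pair equal: only that pair can produce an error, and its own test has level 5%.
- No pair equal: no error is possible.

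The family-wise error is at most 5% in each case. The argument holds for three conditions and not for four or more.

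**3. Critical values at n = 14.** Pooled error on 2 × (14 − 1) = 26 df: Tukey |t| = 2.485 (studentized range ÷ √2), unadjusted |t| = 2.056. A paired test on 13 df uses 2.160.

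**4. Power for low versus control.** Simulated three-condition crossovers, normal data, sphericity, n = 14. The documents give no effect per contrast and no within-person SD, so the effects are assumptions. The first four rows are in SDs of the within-person difference. The last four fix f = 0.6 on the residual SD and vary where the low-volume mean lies.

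| Assumed effects versus control | Tukey alone | Gate + Tukey (plan) | Gate + unadjusted, pooled error | Gate + paired |
|---|---|---|---|---|
| low 0.8, high 0.8 | 0.69 | 0.69 | 0.78 | 0.75 |
| low 0.6, high 0.8 | 0.42 | 0.42 | 0.54–0.55 | 0.52 |
| low 0.6, high 1.0 | 0.42 | 0.42 | 0.57–0.58 | 0.54 |
| low 0.4, high 0.8 | 0.18 | 0.18 | 0.29 | 0.27 |
| f = 0.6, low equals high | 0.80 | 0.80 | 0.87 | 0.85 |
| f = 0.6, low two thirds of high | 0.53 | 0.53 | 0.68 | 0.65 |
| f = 0.6, low half of high | 0.31 | 0.31 | 0.46 | 0.43 |
| f = 0.6, low one third of high | 0.13 | 0.13 | 0.23 | 0.22 |

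Ranges show the spread between simulation runs. Plan against pooled unadjusted is a difference of about 7 to 15 points. Paired tests return about 2 to 3 of these, leaving roughly 5 to 12. The two Tukey columns agree: at f = 0.6 the gate changes Tukey's power by 0.2 points or less. With 12 completers (20 × 0.60), the 0.6 and 0.8 case gives 0.35 against 0.47.

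**5. Only high versus control significant.** With low 0.6 and high 0.8, the probability is about 0.28 as planned and 0.13 with gate plus unadjusted pooled tests (0.16 with paired tests). Tukey without the gate gives 0.29, so the gate does not cause this pattern.

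**6. Error rates, n = 14.**

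| | Gate + Tukey | Tukey alone | Gate + unadjusted | Unadjusted, no gate |
|---|---|---|---|---|
| Family-wise error, all means equal | 0.045 | 0.050 | 0.050 | 0.120 |
| Low equals control, high clearly effective | 0.020 | 0.020 | 0.050 | – |

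**7. Why paired tests.** Without sphericity, an unadjusted test on the pooled error can exceed its level: 0.089 for a truly equal pair in one simulated case, against about 0.05 for the paired test.

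**The case against.** The strongest reply is that nothing here is an error. An omnibus test followed by Tukey is conventional and valid, with family-wise error of 0.045. Some statisticians prefer the stricter control and the simultaneous intervals. That stands, and it is why this is an improvement and not a correction. The size of the gain also depends on assumed effects and on sphericity, which the documents do not supply.

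A reader might infer four stronger points that the documents and figures do not support:

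- **That a double correction causes the loss.** Tukey alone has practically the same power as gate plus Tukey (0.694 against 0.690 with both effects at 0.8). Dropping the gate and keeping Tukey would recover almost nothing.
- **That Tukey brings no error-rate benefit.** It holds a truly equal pair at about 2% instead of 5%, and compared with three ungated unadjusted tests it lowers family-wise error from 12% to 5%.
- **That low volume versus control must be named as the deciding contrast.** The Discussion does say that "if low-volume strength exercise elicits improvement in these parameters, individuals might be more motivated and feel more confident", but that clause names no comparator, and the same sentence opens by giving relevance to low compared with high volume. The Primary objective treats both volumes alike. Ranking the contrasts would be the reviewer's choice, and any ranking could sit in an analysis plan that is not shown.
- **That the trial intends to read non-significance as equality.** Nothing in the article says so, and it plans 95% confidence intervals and effect sizes.

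**Conclusion.** The point holds as a cheap improvement. The planned pairwise rule is valid, but with exactly three conditions Tukey gives up power that closed testing keeps at the same 5% family-wise error within an index. At n = 14 the loss for low versus control is about 7 to 15 points against unadjusted pooled tests, or roughly 5 to 12 points against the paired tests recommended here. The chance that only high versus control is significant is about doubled against the pooled version (0.28 against 0.13).

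These sizes rest on normal data, sphericity, a within-participant ANOVA and assumed effect patterns. The validity of the closed test does not depend on the effect patterns. It does need the omnibus test and each pairwise test to hold its own 5% level. The point concerns contrasts within one index, not the number of indexes.

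**What to change.** In Data analysis, replace the Tukey sentence by wording such as: *If the omnibus within-participant test is significant at 5%, each of the three within-participant contrasts is tested by a paired test (contrast-specific variance) at two-sided 5% (closed test for three conditions). Each contrast is reported with its 95% confidence interval. A non-significant high-versus-low contrast is not interpreted as equal effect.*

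The change needs no new data or participants. All three coded conditions are treated alike, so the analyst can stay blinded. The costs are:

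- Tukey's simultaneous intervals become ordinary 95% intervals.
- The error rate for a truly equal pair rises from about 2% to the nominal 5%.
- Using paired instead of pooled-error tests gives back about 2 to 3 points of power, in return for not relying on sphericity in the pairwise step.
- The rule is valid only while there are exactly three conditions.
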